## Abstract

**Background:**

Although rehabilitation is recommended for terminal cancer patients, the specific components and methods of such programs are poorly documented. No studies to date have examined the effectiveness of rehabilitation for terminal cancer patients. This study aims to evaluate the efficacy of a new intervention for rehabilitation therapists, using the Op-reha Guide (Guide to Optimal and Patient-Centred Rehabilitation Practice for Patients in Palliative Care Units [PCUs]) in rehabilitation practice. This guide consists of recommended actions and attitudes for rehabilitation therapists and aims to optimise therapists’ actions according to the patient’s needs and condition. It shares goals with terminal cancer patients to maintain their activities of daily living (ADL).

**Methods:**

This study uses a multicentre, prospective, randomised controlled trial (RCT) design with two parallel groups in PCUs where specialised rehabilitation will be routinely performed for terminal cancer patients by rehabilitation therapists. Participants will be randomised (1:1) to intervention (the Op-reha Guide) and control groups (usual rehabilitation). We will then conduct an observational study in PCUs that do not perform specialised rehabilitation for terminal cancer patients; this will be considered the usual care group, and the efficacy of usual rehabilitation will be quantitatively evaluated. Inclusion criteria are hospitalisation in PCU, European Cooperative Oncology Group Performance Status of 2 or 3, and clinical estimation of life expectancy of 3 weeks or more. Patients with severe symptom burden will be excluded. We hypothesise that the Op-reha Guide will be more effective in maintaining the ADL of terminal cancer patients hospitalised in PCUs than usual rehabilitation. The primary endpoint is defined as the change in (total) modified Barthel Index from baseline to Day 22. Quality of life will be a secondary endpoint. In total, 135 patients will be recruited from 16 Japanese sites between July 2019 and December 2021.

**Discussion:**

This will be the first trial to evaluate the efficacy of specialised rehabilitation for terminal cancer patients hospitalised in PCUs, and will contribute to the evidence on the efficacy of implementing rehabilitation for terminal cancer patients.

**Trial registration:**

*UMIN-CTR,* UMIN000037298 R000042525 (date of registration 7 July 2019).

## Background

Cancer patients in the terminal phase experience a decline in physical function and activities of daily living (ADL). ADL decline occurs in many cancer patients between 1 and 3 months before death [1, 2]. Many cancer patients wish to maintain their independence even in the terminal phase; thus, the deterioration of physical function and ADL in terminal cancer patients may cause a decrease in their quality of life (QOL) [3, 4]. This is a significant issue for these patients, their families, and healthcare professionals.

In recent years, opportunities for providing rehabilitation to cancer patients have expanded [5]. Cancer rehabilitation is a medical approach that aims to improve cancer patients’ QOL [6] by helping them maintain maximum physical, social, psychological, and vocational functioning within the limits imposed by the disease and its treatment [7]. At the same time, clinical studies on rehabilitation for cancer patients have also increased. These studies have found, for example, that physical exercise for cancer patients has beneficial effects, including improved physical function and reduced symptom burdens [8–19]. However, most participants in these studies were in a disease phase where they could recover their physical function and ADL, such as early mobilisation for perioperative patients, therapeutic exercise during cancer treatments, and physical fitness for cancer survivors, with patients’ prognosis being about 3 to 12 months. In contrast, there are a few studies on rehabilitation that have focused on terminal cancer patients. Moreover, these previous studies in terminal cancer patients were limited to single case reports and surveys on actual situations [20–23]. These studies in terminal cancer patients reported the actual situation of rehabilitation for patients in hospices or palliative care units (PCUs), such as the amount of rehabilitation provided and the content of the implemented rehabilitation programs; they did not exclusively focus on the patients with terminal cancer. More than half the patients in these studies of terminal cancer patients were either alive or had been discharged at the end of the study period. Thus, there were no studies that focused exclusively on patients in the terminal phase.

In other words, although it is recommended that rehabilitation be performed for terminal cancer patients, even during the last days of life [23–25], the effectiveness of rehabilitation for terminal cancer patients has not been evaluated. Furthermore, the specific content and methods of rehabilitation interventions, such as how often, how long, and what kind of rehabilitation should be performed for these patients, are poorly documented. Therefore, rehabilitation therapists currently deliver treatment to patients based on their own experiences; this may cause differences in the quality of rehabilitation provided [26, 27]. In addition, as many cancer patients become increasingly frail in the terminal phase [1, 25], routine interventions might be harmful. Thus, methodologically rigorous studies for the best rehabilitation interventions for terminal cancer patients are urgently needed.

The aim of this study is to evaluate the efficacy of a new, comprehensive guide for rehabilitation therapists, the “Guide to Optimal and Patient-Centred Rehabilitation Practice for Patients in PCUs” (Op-reha Guide), designed to maintain ADL of terminal cancer patients hospitalised in PCUs. An intervention group will receive treatment based on the Op-reha Guide while a control group will receive usual rehabilitation. The study may contribute evidence on the efficacy of implementing rehabilitation with this guide for terminal cancer patients in PCUs.

## Methods

### Design

This study uses a multicentre, prospective, randomised controlled trial (RCT) design with two parallel groups as the RCT arm, and will conduct an additional observational study with a single observational group (usual care) as the observation arm. The study design is summarised in Fig. 1.

**Fig. 1 Fig1:**
[figure not shown]
Flow diagram of the study procedure. Participants will be randomized (1:1 allocation ratio) to Op-reha Guide (intervention group) or usual rehabilitation (control group) in the RCT arm. Assessments will be performed at baseline (T0 randomisation), day 1 (T1), day 8 (T2), day 15 (T3), and day 22 (T4) in RCT and observation arms. Notes. RCT = randomised controlled trial, T = time of assessment, PCU = palliative care unit

In our study, specialised rehabilitation is defined as the treatment provided by rehabilitation therapists, occupational therapists, and physiotherapists. The RCT arm will be conducted in PCUs that routinely perform specialised rehabilitation for terminal cancer patients. The participants of the RCT arm will be randomised (1:1) to the intervention group (the Op-reha Guide) and the control group (usual rehabilitation). The observation group will come from PCUs that do not routinely have rehabilitation therapists perform rehabilitation for terminal cancer patients. The control group will be observed in PCUs where only usual rehabilitation for terminal cancer patients occurs. Observation of the intervention group will occur in PCUs that perform rehabilitation based on the Op-reha Guide. Subsequently, we will compare the patients in the intervention group to those in the control group to discover the effects of using the Op-reha Guide versus usual rehabilitation. We will compare the control group with the observation group to quantitatively evaluate the efficacy of usual rehabilitation. The protocol of this study followed the Standard Protocol Items Recommendations for Interventional Trials (SPIRIT) statement [28] and its checklist.

### Participants and setting

Participants will be recruited from 16 PCUs across Japan. There will be 11 PCUs in the RCT arm and 5 PCUs in the observation arm, and participants will be enrolled according to the inclusion and exclusion criteria. Inclusion criteria are: a) an initial hospitalisation in PCU; b) being 20 years or older at the time when they provide informed consent; c) having a clinical diagnosis of cancer; d) receiving no curative treatment, such as surgery, radiation therapy, or chemotherapy; e) European Cooperative Oncology Group Performance Status (ECOG PS) of 2 or 3; f) having a clinically estimated life expectancy of 3 weeks or more (based on the opinion of investigators and Palliative Prognostic Index of 6 or less); g) starting specialised rehabilitation within 1 week of hospitalisation in PCU (only RCT arm); and h) having the ability to provide written informed consent. Exclusion criteria are: a) having a severe symptom burden (i.e. score of 4 on any of the three Support Team Assessment Schedule items of pain control, other symptom control, and patient anxiety); b) having a respite admission within 1–2 weeks; c) having a weight-bearing limitation due to impending bone fracture; and d) will be undergoing a nerve block anaesthesia or percutaneous vertebroplasty (cement composition).

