### Procedures

#### Enrolment and allocation

Patients hospitalised in PCUs will be screened for eligibility. Eligible patients will be informed of the study procedure, data protection plan, risks, and benefits by investigators. In the RCT arm, each patient who agrees to participate and provides written consent will be randomly allocated to either the intervention group (Op-reha Guide) or the control group (usual rehabilitation). The patients in the RCT arm will start rehabilitation within 7 days after hospitalisation. In the observation group, each patient who agrees to participate and provides written consent will start observation within 7 days of hospitalisation; they will not be randomly allocated.

Data on eligible patients who have given informed consent will be collected and managed using a web-based electronic data capture system in the Japanese Organisation for Research and Treatment of Cancer (JORTC) Data Centre. We used a computer-generated randomisation schedule using stratified permuted block randomisation methods to assign patients to either the intervention or control group in a 1:1 ratio, balanced for the following stratification factors: 1) ECOG PS is 2 or 3; and 2) study site.

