#### Data collection

Assessments will be performed at five time points: enrolment (T0 eligibility and randomisation), Day 1 (T1 baseline), Day 8 (T2), Day 15 (T3), and Day 22 (T4) by investigators consistently at each site. The Day 1 assessment is performed on the day rehabilitation begins in the RCT arm, and on the hospitalisation day within 7 days in the observation group. If a patient is discharged or withdraws before T4, a withdrawal assessment will be performed. If a patient continues to be hospitalised after withdrawal, the remaining measurements will be performed according to the assessment schedule. The follow-up assessment is performed 30 days after T4 or withdrawal. The timing and details of assessments are given in Table 1.

**Table 1 Tab1:** Study procedure and time points for actions and evaluations

	T0 Enrolment	T1 Day1 Baseline	T2 Day 8	T3 Day 15	T4 Day 22	Discharge or Withdrawal	Follow-up30 days after T4 or discharge/ withdrawal
Demographics		x	x	x	x	x	
mBI		x	x	x	x	x	
EORTC QLQ-C15-PAL		x	x	x	x	x	
ECOG PS	x	x	x	x	x	x	
PPS		x	x	x	x	x	
STAS	x	x	x	x	x	x	
PPI	x	x					
Adverse events (RCT)		x	x	x	x	x	
Details of the rehabilitation (RCT)			x	x	x	x	
Reason for stopping (RCT)						x	
Clinical outcome							x

*mBI* modified Barthel Index, *EORTC QLQ-C15-PAL* European Organisation for Research and Treatment of Cancer Quality of Life Questionnaire Care 15 Palliative Care, *ECOG PS* European Cooperative Oncology Group Performance Status, *PPS* Palliative Performance Scale, *STAS* Support Team Assessment Schedule, *PPI* Palliative Prognostic Index, *RCT* Randomised Controlled Trial

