#### Op-reha Guide

The Op-reha Guide is a newly developed intervention guide for rehabilitation therapists designed to address the need to maintain the ADL of terminal cancer patients hospitalised in PCUs. It was developed by integrating both the experience of clinical practice and the literature review by the multidisciplinary team. The team consisted of a rehabilitation therapist (OT and PT), a nurse, a clinical psychologist, and three physicians specialising in palliative care. We also included the opinions of other rehabilitation therapists with expertise in palliative care. The core concepts of the Op-reha Guide are: 1) to optimise the actions and attitude of rehabilitation therapists according to the patient’s needs and condition; 2) to share the goals with the patient; 3) to implement rehabilitation designed to maintain ADL. The Op-reha Guide consists of 22 recommended actions in total; the basic length is 40 min per day, with a frequency of five times per week to adequately perform the actions.

To increase adherence to the protocol intervention and reduce the risk of contamination, we take some measures with the operation method of the Op-reha Guide as follows. First, we will prepare a detailed operational procedure manual and explain the manual in detail for the site investigators at the kick-off meeting, instead of providing training. Only the therapist in charge of patients allocated to the intervention group will be able to access the guide and only for the duration of their intervention. Next, the therapist will receive a recommended list of set actions for each implementation day, with a checklist that must be filled out after each treatment. The therapists may treat both intervention and control group patients but cannot be in charge of the two groups at the same time.

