#### Study population for analyses

The population for efficacy and safety analyses comprises all patients who receive at least one session of the protocol intervention. Patients who are found to be ineligible after registration will be excluded from the efficacy analysis, although they will be included in the safety analysis (adverse events).

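### Inclusion criterion g is worded as an event that follows randomisation, so a late first session can be read as ineligibility and remove a randomised patient from the efficacy analysis

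*Protocol article*

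**What the plan says.** All statements are in the protocol article.

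- **Participants and setting**, inclusion criterion g: "starting specialised rehabilitation within 1 week of hospitalisation in PCU (only RCT arm").
- **Data collection** orders the time points as "enrolment (T0 eligibility and randomisation), Day 1 (T1 baseline), Day 8 (T2), Day 15 (T3), and Day 22 (T4"), and adds: "The Day 1 assessment is performed on the day rehabilitation begins in the RCT arm".
- **Enrolment and allocation** describes allocation after consent and then states the same limit as a matter of conduct: "The patients in the RCT arm will start rehabilitation within 7 days after hospitalisation".
- **Study population for analyses**: the efficacy and safety population "comprises all patients who receive at least one session of the protocol intervention". It continues: "Patients who are found to be ineligible after registration will be excluded from the efficacy analysis". Those patients stay in the safety analysis.
- **Statistical analysis** says that the primary comparison follows intention to treat.
- **Blinding** leaves therapists and other collaborators unblinded.
- **Op-reha Guide**: "The therapists may treat both intervention and control group patients but cannot be in charge of the two groups at the same time". Under Interventions, protocol rehabilitation lasts 3 weeks.

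**The concern.** An inclusion criterion should be settled before allocation. Criterion g refers to the start of rehabilitation, which the schedule places after randomisation. The same 7-day start therefore appears twice, as an entry condition and as a conduct statement about patients already allocated.

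This matters because of the exclusion rule. A late starter has received a session and so belongs to the treated population. Only criterion g, applied through the exclusion of patients found ineligible after registration, could remove that patient. The removal would rest on something that happened after allocation, under staff who know the allocation, in a comparison described as intention to treat. Patients who start late because they deteriorated would also be expected to have a different course of activities of daily living from the rest. At stake are the protection given by randomisation and some power.

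**Working it through.** **Order of events.** Three places, side by side:

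| Step | Where stated | When |
|---|---|---|
| Eligibility check and randomisation | Data collection | T0 |
| First session | Data collection | T1 (Day 1) |
| Start within 1 week as entry criterion | Participants and setting, g | judged at T0, but met or failed at T1 |

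T0 and T1 may fall on the same day. That shortens the gap but does not reverse the order. For example, a patient randomised on hospital day 5 whose first session slips to day 9 passes everything that can be observed at T0 and fails g as literally worded at T1.

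**Planned sample size (Sample size calculation).** Inputs: difference 10, SD 15, two-sided 5%, power 80%, attrition 15–20%. The normal approximation gives n = 2 × (1.96 + 0.84)² × 15²/10² = 35.3, rounded up to 36 per group. At 20% attrition, 36/0.80 = 45 per group, 90 in total. The stated figure reproduces and is not in dispute.

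**Power if late starters are excluded on top of attrition.** The documents give no late-start share, so the shares below are assumptions. Patients analysed per group = 45 × (1 − attrition) × (1 − late share).

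| Late share excluded | Power at 15% attrition | Power at 20% attrition |
|---|---|---|
| 0% | 83.0% | 80.7% |
| 5% | 81.1% | 78.7% |
| 10% | 79.0% | 76.5% |
| 15% | 76.7% | 74.1% |

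**Bias if exclusion falls on one group only (assumption).** If a share f of a group is removed and those patients' mean change differs by D points from that of the patients who remain, the group mean shifts by f × D. With f = 10% and D = 10 the shift is 1.0 point. With f = 20% and D = 15 it is 3.0 points. The target difference is 10.

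**How often could the therapist rule delay a start?** Assumptions: 90 patients spread evenly over 11 sites and 30 months (July 2019 to December 2021, about 130 weeks), 3 weeks on treatment each, half of them in the other group. Even accrual is a simplification, since Status of the trial reports a quarter of patients enrolled after the first year.

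- Patients per site: 90/11 = 8.18. Rate: 8.18/130 = 0.063 per week.
- Expected number on treatment when a new patient arrives: 0.063 × 3 = 0.189, of whom 0.189/2 = 0.0945 are in the other group.
- One therapist per site: 1 − exp(−0.0945) = 9.0%, and 0.090 × 90 = about 8 patients.
- Two therapists per site: a conflict needs both to be in charge of other-group patients, so the chance is at most 1 − exp(−0.0945) × (1 + 0.0945) = 0.4%, and 0.004 × 90 = about 0.4 patients.

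The number of therapists per site is not given. The calculation counts overlap on arrival. It takes no account of the days left in the 7-day window or of patients who stop early, so it counts possible conflicts, not late starts.

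**The case against.** The strongest reply is that g means a planned start. The criteria are written in participles, exclusion d in the same list is openly about the future, and staff could certify at T0 that rehabilitation is due within the week. That reading is available, and on it no event after allocation decides entry. But the text does not say planned or expected, and sites could apply it differently. The ambiguity stands.

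Second, no section states that a late starter is ineligible. This is right: it is an inference from criterion g and the exclusion rule taken together. The wording permits it and nothing rules it out.

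Third, the bias arises only through the analysis population. This also stands. A reader might infer that the criterion would damage the comparison even if the analysis population were corrected. It would not: if every randomised patient is analysed as allocated, a late start removes nobody, and only a wording fault remains.

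Fourth, a reader might infer that allocation decides eligibility differently in the two arms. The documents do not show this. The therapist rule is symmetric under 1:1 allocation, waiting for a therapist is not in itself linked to prognosis, and nothing connects the 40- and 20-minute session lengths with a delayed first session.

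**Conclusion.** The point holds as a fault of wording with an avoidable consequence for the analysis. As written, criterion g together with the exclusion of patients found ineligible after registration lets a randomised patient be dropped for a post-allocation event that unblinded staff and the therapist rule may influence. That conflicts with the stated intention-to-treat principle.

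The size cannot be determined from the documents. A reader might take the figure of 8 of 90 as an expected loss, but it needs exactly one therapist per site, falls below 1 with two, and counts possible conflicts only. Under the assumed shares, excluding 5–10% late starters at 20% attrition lowers power from 80.7% to 78.7–76.5%. A one-sided exclusion of 10% with a 10-point difference moves a group mean by 1.0 point. These effects are modest. The change is worth making because it costs almost nothing and protects the randomised comparison.

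**What to change.** 1. Reword criterion g as a planned start of specialised rehabilitation within the existing window, judged at T0 before randomisation. The window itself is not changed.
2. Keep the 7-day start under Enrolment and allocation as a conduct target.
3. State under Study population for analyses that an actual later start is a protocol deviation, recorded with date and reason, and is not ineligibility found after registration. The patient stays in the primary analysis as randomised.

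The cost is one reworded criterion and one sentence on the analysis population. A few late starters will remain in the analysis and may dilute the effect slightly. Because Day 1 is counted from the first session, they can still follow the full assessment schedule. How sites arrange therapist cover is operational detail that an article may leave to the procedure manual, and this point does not depend on it.

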### Measurement tools

#### Modified Barthel Index (mBI)

The mBI [29] is a modified version of the Barthel Index (BI) and uses a 5-point scale, which is more sensitive to changes in the ability to perform ADL than the BI [30]. The BI assesses 10 daily tasks: personal hygiene, feeding, bathing self, dressing, toilet, bowel control, bladder control, chair/bed transfers, ambulation, and stair climbing. The mBI reflects the level of independence, from 0 (*needs full assistance*) to 100 (*independence*). The reliability and validity of the Japanese version of mBI have been confirmed [31, 32].

#### European Cooperative Oncology Group Performance Status (ECOG PS)

The ECOG PS includes six grades, from 0 (*fully active*) to 5 (*died*), to assess how the disease affects the daily living abilities of the patient [33].

#### Palliative Performance Scale (PPS)

The PPS comprises 11 levels, from 0% (*death*) to 100% (*full*), to assess a patient’s ambulation, activity and evidence of disease, self-care, intake and consciousness level [34, 35]. The PPS is also used as a prognostic tool to estimate the survival in palliative care patients [34, 36].

